#### Therapy Process Outcomes

##### The Parent and Child Satisfaction Scales (PCSS)

The PCSS (Hawley and Weisz, 2005) is an eight-item questionnaire assessing satisfaction with mental health services. Items are rated on a 4-point scale. Higher total scores indicate higher satisfaction.

##### The Therapeutic Alliance Scale for Children (TASC)

The TASC (Shirk and Saiz, 1992) is a nine-item scale measuring the quality of the youth's working alliance with their clinician. Items are rated on a 4-point scale from 1 (very true) to 4 (very false). Sum scores are calculated by reverse scoring negative items so that lower scores indicate higher working alliance.

##### The Therapist Satisfaction Inventory (TSI)

The TSI (Addis and Krasnow, 2000) is a 16-item questionnaire measuring clinician satisfaction with their treatment approach. Items are rated on a 5-point scale from 1 (strongly disagree) to 5 (strongly agree). Higher scores indicate higher satisfaction.

##### Evidence-Based Practice Attitudes Scale (EBPAS)

The EBPAS (Aarons, 2004) is a measure assessing clinician attitudes toward evidence-based practices. The EBPAS is comprised of four subscales: (a) Appeal, (b) Requirements, (c) Openness, and (d) Divergence and a total scale score representing global attitude toward adoption of evidence-based practices. Clinicians respond to items on a 5-point scale from 0 (not at all) to 4 (to a very great extent), with higher scores indicating more positive attitudes.

#### Academic Outcomes

##### Academic Competence Evaluation Scales (ACES)

The ACES (DiPerna and Elliott, 1999) is a 73-item measure assessing academic skills (Reading/Language Arts, Mathematics, and Critical Thinking) and enabling behaviors (Interpersonal Skills, Engagement, Motivation, and Study Skills). Teachers provide ratings for both proficiency and importance of each skill. Proficiency ratings are on a 5-point scale from 1 (far below grade-level) to 5 (far above grade-level). The importance of a particular skill is measured on a 3-point rating scale from l (not important) to 3 (critical). Confidence bands are created around raw scores at the 90% confidence interval for each scale and subscale. Bands may fall in the “Developing,” “Competent,” or “Advanced” range.

##### The National Survey of American Families School Engagement Scale (NSAF)

The NSAF (Ehrle and Moore, 1999) is a measure of behavioral, emotional, and cognitive engagement in school. Respondents rate the youth's interest and willingness to do schoolwork on a 4-point scale from 1 (none of the time) to 4 (all of the time). Scores are summed to create a 16-point scale, with higher scores indicating greater school engagement.

##### The School Engagement Measure-MacArthur Network (SEM)

The SEM (Fredricks et al., 2005) is a 15-item measure of school engagement and consists of three engagement scales: (a) Behavioral, (b) Emotional, and (c) Cognitive. Items are rated on a 5-point scale from 1 (never) to 5 (most of the time). Sum scores are calculated by reverse scoring negative items so that higher scores indicate higher school engagement.

### Statistical Analysis

Primary data analyses for the study will involve a multilevel modeling (MLM) approach using HLM 7 (Raudenbush et al., 2011), with repeated measures (Level 1) nested within youth (Level 2) nested within clinicians (Level 3). Because school-level variables are not of conceptual interest in the analyses and due to the relatively small number of schools, school-level nesting will be incorporated by dummy coding schools and entering them as predictors of the Level 3 intercept. Multiple imputation or full information maximum likelihood estimation will be used to accommodate data that are missing at random.

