### Trial Design

This is a multi-site RCET comparing MATCH to UC in existing school-based clinical settings. After obtaining written informed consent, clinicians are randomized to implement MATCH or to provide the care that they typically use and believe to be effective (i.e., UC). Block randomization is used to assign clinicians to a treatment condition in a 1:1 ratio to balance representation across conditions in each school (Weisz et al., 2009; Friedman et al., 2010). MATCH clinicians complete training in MATCH and PATH during the summer preceding the first academic year of their involvement in the study. Trainings, conducted by MATCH experts, include didactic presentations (e.g., on flowcharts, modules), trainers' modeling of MATCH treatment components, video clips showing modules being delivered by clinicians, role plays, and discussion. Clinicians randomized to the UC condition will receive MATCH training after all 6-month follow-up data collection is complete. Randomization will not occur at the youth-level because many youths seen in schools commonly (1) have an existing relationship with a particular clinician (i.e., disrupting an existing therapeutic relationship could be harmful) and/or (2) are assigned to particular clinicians based on grade level or school case assignment policy that cannot be changed.

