## Methods and Analysis

### Participants

This study takes place across 27 K-8 schools in five Boston-area school districts. The protocol is designed to be useful for any school-based mental health service provider (referred to as “clinicians”), regardless of their professional affiliation (e.g., psychologists, social workers, guidance counselors, nurses, interns) or level of training (e.g., trainee, licensed, or unlicensed). Study clinicians include those employed by school districts and those employed by outpatient clinics that have contracts with districts to provide services in the schools. Participating youths are aged 7–14 (grades 3–7), similar to the age range in previous MATCH trials (Weisz et al., 2012; Chorpita et al., 2013, 2017). Participating youths include those who are: (1) referred by school personnel for counseling or mental health services, (2) identified by school personnel and/or caregivers as being at risk of needing special education services for emotional and/or behavioral difficulties, (3) receiving special education services for emotional and/or behavioral difficulties, or (4) receiving special education services due to another disability and participating in school-based mental health services. Youths are eligible for the study if they or their caregivers endorse clinically elevated problem levels on standardized measures of depression, anxiety, disruptive conduct, post-traumatic stress, or any combination thereof. Youths are excluded from the study if they present only with concerns outside the scope of MATCH, including problems of inattention and/or hyperactivity, intellectual disability, pervasive developmental disorder, psychosis, or eating disorders, or if they had undergone psychiatric hospitalization within the year prior to baseline assessment. Teachers are invited to participate in the study (one teacher per youth) by completing study measures related to their student (Table 1).

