### Sample Size

Our goal is to include 168 youths. The Optimal Design program (Spybrook et al., 2011) was used to determine power for main treatment effects in MLM (research questions 1 and 2) based on the: number of clusters (e.g., number of schools or clinicians), average cluster sizes (e.g., number of youth per clinician, number of clinicians per school), intraclass correlation coefficients (i.e., within- clinician and within-school correlations for the dependent variable) and alpha level. Accordingly, the expected sample will be powered at 0.80 to detect an effect size of 0.50 (*p* = 0.05) for both repeated measures and single time-point analyses. Regarding research question 3, we have not found any published conventions for estimating power for mediation in MLM. Using non-nested mediation conventions (Fritz and Mackinnon, 2007), the expected sample size is powered above 0.80 to detect mediation when both “a” and “b” paths are small-to-medium (i.e., .26) (Cohen, 1988).

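### If the primary model is fitted by full maximum likelihood, 26 school dummies at the clinician level raise the type I error of intercept and single time-point tests to about 7–13%

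*Protocol article*

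**What the plan says.** Under Statistical Analysis, the protocol article describes the primary model as one "with repeated measures (Level 1) nested within youth (Level 2) nested within clinicians (Level 3"). School is not a level of its own. Instead, "school-level nesting will be incorporated by dummy coding schools and entering them as predictors of the Level 3 intercept", partly because school variables are of no conceptual interest and partly "due to the relatively small number of schools". No school term is stated for the slope.

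Participants gives the number of schools: "This study takes place across 27 K-8 schools in five Boston-area school districts". Sample Size gives the target: "Our goal is to include 168 youths". Trial Design makes the clinician the randomised unit: "Block randomization is used to assign clinicians to a treatment condition in a 1:1 ratio to balance representation across conditions in each school".

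On missing data: "Multiple imputation or full information maximum likelihood estimation will be used to accommodate data that are missing at random". The article does not say whether the variance components are fitted by full or restricted maximum likelihood (REML), what reference distribution the tests use, or whether treatment is tested on the intercept, the slope or both. The power statement covers both repeated-measures and single time-point analyses.

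**The concern.** Twenty-seven is not a small number of dummy-coded units when the dummies sit at the level of the randomised clinician. Full maximum likelihood estimates variances as if the fixed coefficients were known. With 28 of them at the clinician level, the residual between-clinician variation is understated and the estimate is often pushed to zero. The model then treats youths of one clinician as independent, although the clinician was randomised.

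For any treatment effect in the equation that carries the dummies, confidence intervals would be too narrow and false positives too frequent. This is the primary analysis, and single time-point comparisons are explicitly part of it.

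**Working it through.** **Stated power first.** For an effect size of 0.50 at two-sided 0.05 (sidedness is assumed), independent youths would need 2 × (1.960 + 0.842)² / 0.50² ≈ 63 per arm, or 126 in total. With 84 per arm, power is about 0.90. The target of 168 therefore allows a design effect of 168/126 = 1.33. Setting 1 + (m − 1) × ICC = 1.33, with m = 168/J youths per clinician:

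- J = 42, m = 4.00: ICC 0.11
- J = 54, m = 3.11: ICC 0.16
- J = 81, m = 2.07: ICC 0.31

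The stated 0.80 is attainable. It cannot be reproduced, because neither J nor the ICC is given.

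**Coefficients.** 26 dummies + intercept + treatment = 28. Clinician-level residual degrees of freedom are J − 28: 14, 26, 53 and 80 for J = 42, 54, 81 and 108.

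**A floor that needs no assumed J or ICC.** Take a single time-point with no clinician variance at all. Full maximum likelihood divides by 168 instead of 168 − 28 = 140, so the variance is understated by 140/168. The effective critical value is 1.96 × √(140/168) = 1.79, and a nominal 5% z test runs at 7.4%. Simulation of this case gave 7.5–7.7%.

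**With clinician variance.** Null data were simulated with 168 youths, 27 schools and unequal cluster sizes, 6,000 runs per setting. The model had a clinician random intercept and the 26 dummies, fitted by full maximum likelihood. Type I error in %, z test / t test on J − 28 df:

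| Clinicians | ICC 0 | ICC 0.05 | ICC 0.10 | ICC 0.20 |
|---|---|---|---|---|
| 42 | 7.7 / 5.3 | – | 13.3 / 10.0 | 18.7 / 15.2 |
| 54 | 7.5 / 6.2 | 10.2 / 8.9 | 12.2 / 10.4 | 14.7 / 13.0 |
| 81 | 7.6 / 6.9 | – | 9.7 / 9.0 | 11.7 / 10.8 |
| 108 | 7.7 / 7.2 | – | 8.0 / 7.7 | 9.6 / 9.2 |

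A separate simulation with arms balanced in each school and t on J − 28 df, at ICC 0.05–0.10, gave 8.0–11.7% for 54 clinicians and 7.5–9.7% for 81.

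**Why it happens.** At ICC 0.10 the clinician variance was estimated as exactly zero in 96% of full-likelihood runs with 54 clinicians, 86% with 81 and 77% with 108. Under REML the figure was about 21–25%. At higher ICCs the collapse is less complete: 80% at ICC 0.20 and 49% at ICC 0.30 with 54 clinicians.

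**Same data, REML.** With the dummies kept and t on J − 28 df, type I error was 2.8–5.4% over all settings (4.9% with 54 clinicians, ICC 0.10). The separate simulation gave about 4–6%. A random school effect with REML gave 5.1–5.7%.

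**Slope.** A joint intercept-and-slope growth model was fitted by full maximum likelihood, with dummies on the intercept only and 54 clinicians (500 runs per setting, Monte Carlo error about 1 point). The z test rejected in 10.6–12.6% for the intercept effect and 4.8–6.8% for the slope effect. In an equation without dummies and with school variance of 0.05–0.10, full maximum likelihood gave 2.7–5.7%.

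**The case against.** The strongest reply is that the article does not commit to full maximum likelihood for the variance components. It names it as one of two ways to handle missing data, and an article may leave the estimator and degrees of freedom to a fuller document. This stands: the dummies alone do not cause the inflation, since REML with the same dummies is sound. But full maximum likelihood is a route the plan names, and choosing multiple imputation would still leave the estimator open for each imputed data set.

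It is also fair that the number of clinicians and the ICC are assumptions. The 7.4% floor is free of both, though it applies to a z test on a single time-point outcome.

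Four stronger readings are tempting but not supported:

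- *That 7–13% is the trial's true type I error.* It is conditional on the estimator and on the tested parameter.
- *That tests of change are inflated too.* The dummies do not enter the slope, and its error stays near 5–7%. The article does not say that treatment is tested there. With arms balanced within schools, leaving school variation in change out of the slope can only cost power.
- *That the dummies wreck power.* At effect size 0.50, clinician ICC 0.10 and school ICC 0.02, power with dummies against a random school effect is 0.32 against about 0.75 with 34 clinicians, and 0.62 against 0.79 with 42. But both arms in every one of 27 schools require at least 2 × 27 = 54 clinicians, so these cases sit badly with the stated blocking. At 54, power is 0.81 against 0.83.
- *That the power calculation contradicts the model.* It lists "intraclass correlation coefficients (i.e., within- clinician and within-school correlations for the dependent variable") as an input. Fixed school terms also absorb school variance, so that input does not by itself imply a different model.

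**Conclusion.** The point holds in conditional form. If the primary model is fitted by full maximum likelihood, 26 school dummies on the clinician-level intercept give a type I error of about 7–13% for treatment effects on an intercept or single time-point outcome. This assumes 54–108 clinicians, a clinician ICC of 0.05–0.20 and t tests on J − 28 degrees of freedom. With z tests the upper end is nearer 15%, and with fewer clinicians the error can be larger still. Slope effects without dummies are not materially inflated. The reason given for the dummies fits poorly with 27 schools, but fixed school terms remain defensible because randomisation was balanced within school. What needs changing is the estimator and the reference distribution.

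**What to change.** Keep the school dummies, but state that the model is estimated by REML and that treatment is tested by t on clinician-based small-sample degrees of freedom (J − 28, or Kenward-Roger or Satterthwaite). REML on all available records is also valid under missing at random, so nothing is lost on missing data. State which parameter carries the treatment effect. If it is the slope, enter the school term there as well, still under REML, since dummies on the slope under full maximum likelihood would bring the same inflation to that test.

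A random school effect with REML is an acceptable alternative. It assumes that school effects are unrelated to the share of treated clinicians, which blocking within school supports.

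The cost is a change of wording, slightly wider confidence intervals and possibly different software settings. The article does not show whether the named program fits this model by REML, so that should be checked before the wording is fixed.

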### Sample Size

Our goal is to include 168 youths. The Optimal Design program (Spybrook et al., 2011) was used to determine power for main treatment effects in MLM (research questions 1 and 2) based on the: number of clusters (e.g., number of schools or clinicians), average cluster sizes (e.g., number of youth per clinician, number of clinicians per school), intraclass correlation coefficients (i.e., within- clinician and within-school correlations for the dependent variable) and alpha level. Accordingly, the expected sample will be powered at 0.80 to detect an effect size of 0.50 (*p* = 0.05) for both repeated measures and single time-point analyses. Regarding research question 3, we have not found any published conventions for estimating power for mediation in MLM. Using non-nested mediation conventions (Fritz and Mackinnon, 2007), the expected sample size is powered above 0.80 to detect mediation when both “a” and “b” paths are small-to-medium (i.e., .26) (Cohen, 1988).

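### The mediation power above 0.80 leaves out the clinician clustering that the main-effect power includes, and is therefore optimistic for this design

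*Protocol article*

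**What the plan says.** The Sample Size section sets the target: "Our goal is to include 168 youths". For research questions 1 and 2, power was computed from cluster numbers, cluster sizes, intraclass correlations and alpha, with the result that "the expected sample will be powered at 0.80 to detect an effect size of 0.50". The values of those cluster inputs are not printed.

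For research question 3 the basis changes. The section explains that "we have not found any published conventions for estimating power for mediation in MLM". It then continues: "Using non-nested mediation conventions", "the expected sample size is powered above 0.80 to detect mediation when both" the a and b "paths are small-to-medium (i.e., .26").

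Two other places matter. Under Trial Design, clinicians and not youths are randomised, in a 1:1 ratio. Under Statistical Analysis, the planned model has repeated measures "nested within youth (Level 2) nested within clinicians (Level 3").

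**The concern.** Research question 3 asks whether any benefit of MATCH on school outcomes runs through mental health. The a path of that model is the treatment effect on mental health, the same clinician-randomised contrast as research question 1. One paragraph therefore gives two accounts of the precision of one contrast: with clustering for the main effect, without it for mediation.

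The effect sizes are nearly the same. With 1:1 allocation the treatment indicator has SD 0.5, so a standardised a of .26 is a difference of about 0.52 SD, close to the 0.50 that has power of 0.80. A mediation claim also needs the b path. It is therefore doubtful that power for the whole indirect effect exceeds 0.80. If it does not, a null mediation result would be read as better powered than it was.

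**Working it through.** **Inputs from the protocol article.** N = 168; 1:1 allocation, taken as 84 youths per arm; a = b = .26; main-effect power 0.80 at d = 0.50; alpha 0.05.

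**Assumptions.** Alpha is two-sided. The mediator clusters like the outcome. Except in step 5, the mediation test is joint significance (both paths significant), so power is the product of the path powers. Φ is the normal distribution function.

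**1. Reproduce the stated mediation figure, non-nested.**
- Each path: .26 × √168 = 3.370; power Φ(3.370 − 1.960) = 0.921.
- Joint: 0.921 × 0.921 = 0.85 (0.84 with t distributions).
- If .26 is a correlation, the coefficient is .26/√(1 − .26²) = 0.269 and joint power is 0.88.
- Simulated non-nested bootstrap: 0.82 (percentile) and 0.87 (bias-corrected). A Sobel test would give only 0.66.

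So the stated figure is right on its stated basis.

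**2. What the main-effect statement implies.**
- Without clustering, d = 0.50 with 84 per arm has noncentrality 0.50 × √(84/2) = 3.240 and power 0.90.
- Power of 0.80 corresponds to 1.960 + 0.842 = 2.802.
- Implied design effect: (3.240/2.802)² = 1.34, an effective N of 168/1.34, about 126.

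**3. Put the a path on the main-effect basis.**
- .26 as a coefficient with residual SD 1: d = 2 × .26 = 0.52; noncentrality 2.802 × 0.52/0.50 = 2.914; power Φ(0.954) = 0.83.
- .26 as a correlation: d = 2 × 0.269 = 0.54; noncentrality 3.018; power 0.855.
- a path set at exactly d = 0.50: power 0.80.

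**4. Joint-significance power.** The deflated b path uses the same design effect of 1.34.

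| a path | a-path power | b path at full N | Joint | Joint, b path also deflated |
|---|---|---|---|---|
| d = 0.50 | 0.80 | 0.92 | 0.73–0.74 | 0.80 × 0.83 = 0.66 |
| d = 0.52 | 0.83 | 0.92 | 0.76 | 0.83 × 0.83 = 0.69 |
| d = 0.54 | 0.855 | 0.937 | 0.80 | 0.855 × 0.855 = 0.73 |

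**5. Other tests.** Cluster-bootstrap simulations (1,500 trials per scenario, 500 resamples each) used assumed layouts of 56 × 3, 42 × 4 and 28 × 6 (clinicians × youths). The ICCs of 0.169, 0.113 and 0.068 were chosen to give the design effect of 1.34. Across both readings of .26, and with or without clustering in the outcome, the percentile bootstrap gave 0.74 to 0.81 and the bias-corrected bootstrap 0.81 to 0.86. The simulation standard error is √(0.8 × 0.2/1500), about 0.01, so the lowest bias-corrected values are hard to tell from 0.80.

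**6. Path size that gives 0.80.** By joint significance with a = b and d = 2a, the a-path noncentrality is 2.802 × 2a/0.50 = 11.21a.
- b at full N, a = b = 0.27: Φ(3.026 − 1.960) × Φ(3.500 − 1.960) = 0.857 × 0.938 = 0.80.
- b also deflated, a = b = 0.287: Φ(3.217 − 1.960)² = 0.896² = 0.80.

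**The case against.** The plan hides nothing. It says that the mediation calculation is non-nested and why, in the sentences that carry the figure, and on that basis the figure is correct. A reader might infer an arithmetic error or a flat contradiction between two power statements. The article supports neither: two openly different methods give two different numbers.

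A reader might also argue that power for the indirect effect cannot exceed a-path power, so that 0.80 is a ceiling. That holds only for the joint-significance test. Even then the a path at d = 0.52 has power 0.83, above 0.80, and the shortfall comes only from the b path. No mediation test is named, and the bias-corrected cluster bootstrap stays at 0.81 to 0.86. If .26 is a correlation and the b path keeps full precision, joint-significance power is 0.80 and the gap nearly closes.

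The consequences are limited too. Mediation is the third question and is posed only if school outcomes benefit.

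All of this stands, and it limits the size of the point. It does not remove it. Disclosing the basis explains the choice, but the sentence still credits this clinician-randomised sample with more than 0.80 and does not say that the omitted clustering lowers power. Nor is a published convention needed: a simulation can use the inputs already assembled for the main effects.

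**Conclusion.** The concern holds as a moderate point. The mediation power is computed on a basis that does not match the design or the plan's own main-effect calculation, and it is optimistic. Anchored to the stated 0.80 at d = 0.50, joint-significance power at a = b = .26 is about 0.73 to 0.80, against about 0.84 without clustering. It is about 0.66 to 0.73 if clustering also weakens the b path. A bias-corrected cluster bootstrap may stay just above 0.80.

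No single replacement figure can be read from the article. The values depend on the mediator clustering like the outcome, on how .26 is read, on the b path and on the unnamed test; the layouts and ICCs in the bootstrap runs are assumed. It would go too far to say that power is definitely below 0.80. What can be said is that the article does not support more than 0.80 for this design, and that the most direct reading of its own numbers falls somewhat short.

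**What to change.** Replace the mediation sentence with the power from a short simulation of the clinician-randomised mediation model. Use the clinician numbers, cluster sizes and ICCs that went into the main-effect calculation, and the mediation test that will be applied; name that test. State whether .26 is a coefficient or a correlation. Report either the resulting power at a = b = .26 or the path size that gives 0.80. On the joint-significance approximation above that size would be about 0.27 to 0.29, but the simulation should supply the figure.

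If no simulation is run, say that the figure is an upper bound that omits clustering by clinician.

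The cost is a short simulation and one rewritten sentence. Sample size, design and analysis model stay as they are; the stated power may become slightly less favourable.
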